1  
2  
3  
4  
5  
6  
7  
8  
9  
10  
11

Patient Perceptions of Hospital Admission Interviews

[name]

Department of Psychological Medicine, The University of Auckland

[name]

Introduction

The recent emphasis on the provision of person-centred healthcare calls upon the health system and its service providers to recognise patients as human beings with complex needs, both psychologically and physically. Existing systems and processes within the health system often result in systematic dehumanisation of patients (Karan, 2019). By depersonalising the individual human experience via labelling the person as a patient with condition x, clothing them in revealing and anonymising patient hospital gowns, placing tags on their wrists and placing them in non-stimulating patient wards, people are psychologically prepped to take on the patient role, be vulnerable and to hand power over their care to their physicians (Haslam & Loughnan, 2014; Morton et al., 2020). This is especially true in the context of secondary or specialist care in New Zealand where patient hospital gown wearing, wrist tagging and provision of a bed, is standard practice upon admission. If New Zealand, like many other nations around the world, would like to improve the quality and experience of care provided in order to improve health outcomes, then experiences of dehumanisation in healthcare must be considered.

Dehumanisation has many operationalisations across various areas of research. In the context of healthcare and medicine, dehumanisation becomes important to consider as it highlights a situation in which patient agency and experience is impacted. Dehumanisation in healthcare takes place because systems and service providers fail to consider the mental states of its patients. Hence, dehumanisation in this context refers to mechanistic forms of dehumanisation rather than the malicious and animalistic treatment of patients by healthcare providers and systems (Haque & Waytz, 2012). Mechanistic dehumanisation according to Haslam (2006)'s Dual Model of Dehumanisation occurs more within interpersonal interactions and within organisational settings and are often a result of unconscious and

37 automatic processes. Those experiencing this form of dehumanisation will often be denied  
38 qualities of warmth, emotion, and individuality (Christoff, 2014; Haslam & Loughnan, 2014).

39 In treating people more as objects and less as humans, it is argued that people enter into  
40 “cognitive deconstructive” states, which are often embodied by emotional numbness,  
41 cognitive inflexibility, and thoughts with reduced clarity and meaning (Christoff, 2014).

42 These cognitive states could lead to low mood and feelings of sadness. Further, people may  
43 accept a lower status and experience emotions of shame and guilt. In this way, experiencing  
44 mechanistic dehumanisation could have a significant negative impact on a person’s  
45 psychological health. Self-determination theory proposes that basic psychological needs such  
46 as competence, autonomy and relatedness must be met to be psychologically healthy (Ryan &  
47 Deci, 2000). When such needs are unmet, people are more likely to experience mental  
48 illnesses like anxiety, depression, and stress-related conditions (Christoff, 2014).

49 Research also highlights that dehumanisation of patients is more likely to result in provision  
50 of non-empathetic and non-compassionate care and can negatively impact patient outcomes  
51 (Halpern & Weinstein, 2004; Haque & Waytz, 2012; Haslam & Loughnan, 2014). Given  
52 scarce healthcare resources, system managers and providers are forced to do more with less  
53 and are constantly pushed to sacrifice humanising communication and behaviours such as  
54 taking time to learn about the patient’s family and what is important to them, in order to  
55 carefully manage scarce resources and reach funding targets. In such situations, the quality of  
56 the healthcare service is severely impacted by the systemic pressures placed on service  
57 providers. In addition to these systemic factors, routine procedures such as patient gown  
58 wearing has also been increasingly explored to understand its impact on experiences of  
59 dehumanisation for patients. This research protocol looks to further this area of research via  
60 the proposed study.

Patient gowns, especially in the hospital setting, were first introduced to better support infection control, for easy mobility, and to increase easy access to the patient's body for the purposes of physical examination and undertaking medical and surgical procedures. Today, most hospital stays, as well as certain medical services such as imaging, will require patients to strip-off and wear a pre-worn backless gown. These gowns often do not accommodate different body shapes and sizes and are not designed to reflect the varying cultural beliefs and values which exist across diverse patient populations.

Research and theory highlights that what people wear is an expression of themselves, a self-representation, and an indicator to those around them about who they are and what matters to them (Tombs, 2011). Clothing helps people get into the role of who they want to be and how they want to be perceived. In this way, clothing is often argued to be a social tool supporting the person to feel confident and competent (Piacentini & Mailer, 2004). Adam and Galinsky (2012) propose that when considering the impact of clothing on psychological processes, both the clothing's symbolic meaning and the physical experience of wearing it must be evaluated. Boddington et al. (2021)'s research across the United Kingdom supports this theory. In this study the authors looked at the experience of people with dementia wearing hospital attire. The results showed that people experienced distress after wearing hospital clothing, especially when considering how others perceived them. The study argues that clothing worn in the hospital has a significant impact on maintaining dignity, autonomy, and humanness.

Given the importance of clothing in maintaining one's identity, self-confidence, and self-esteem, it is very important to consider the psychological impact of gown wearing for patients in healthcare settings. This is especially true if patient hospital gown wearing creates an experience of dehumanisation impacting health outcomes.

Research investigating the impact of patient hospital gowns on the dehumanising experiences in healthcare settings is scant. Most studies in this area have utilised qualitative (mostly interviews) or mixed methods (interviews and surveys) designs to understand both patient and service provider perspectives. For patients, their privacy and dignity are impacted as the hospital gowns often require assistance to wear properly. Even after assistance to dress, the gown's backless design means they sometimes bare all as they walk the corridors of the hospital. The gown is often seen as a metaphor for illness, and once worn, invites the wearer to accept their lowered status as a patient and hand power over their mind and body to their carers as they take on the role of the sick and vulnerable (Jankovska & Park, 2019; Topo & Iltanen-Tähkävuori, 2010; Wellbery & Chan, 2014).

A study by Lucas and Dellasega (2020) showed that patients found gown wearing to be a disempowering process driven by provider needs. Providers in this study expressed guilt for putting accessibility concerns over patient comfortability and dignity. Further, providers shared that seeing patients in gowns provoked biases in the way they thought about the patients and their situations. This finding mirrors findings from other studies on perceptions patients have of healthcare providers and their attire, especially doctors wearing white coats. Patients perceive doctors wearing white coats to be of higher status and more powerful (Jennings et al., 2016). This research supports the theory that clothing has a direct impact on psychological processes for people in the context of healthcare.

Findings from previous research indicates that wearing a patient gown can indeed be a depersonalising and arguably a dehumanising experience. Whilst the gown serves important functions in the healthcare setting, the psychological impact of gown wearing must be considered if the health system is to provide more person-centred healthcare services to promote positive health outcomes.

The negative psychological effects of wearing a patient gown may impact physical health outcomes through behavioural and neuro-immune pathways. Research has shown direct links between stress, immune function, behaviour, physical health, and mental health outcomes (Tausk et al., 2008; Zachariae, 2009). Hence, if patients are feeling vulnerable and lack self-confidence, this could impact their overall health and wellbeing. For instance, a person admitted following a fall may feel more fragile and vulnerable in the hospital gown. This could impact how well they do on assessments for discharge and how strong and safe they feel to go back home.

The patient gown can impact the doctor-patient relationship as highlighted previously. Patients take on a lower status and accept carers as more powerful once gowned, and physicians are unable to gather any personal information from patient attire about who the person in front of them is. Hence, both patient and provider behaviour may be impacted and reflected in overall patient outcomes (Morton et al., 2020). It is also interesting to note that some research has also identified that gown wearing is not always required for certain healthcare contexts, yet patients are still requested to change into gowns. This highlights the need to re-evaluate routine practices in some contexts (ref).

Given the very limited research exploring the impact of hospital gowns on dehumanising experiences in healthcare, this study hopes to extend what is known via conducting experimental research in this area that could allow conclusions around causation to be made more confidently. Using an experimental study design, this research will investigate the extent to which patient attire, specifically the hospital patient gown, contributes to the dehumanisation experience of patients. It is hoped that this study will help raise awareness of the effects gown wearing has on patient psychology.

As health systems around the world move towards a more person-centred model of healthcare, it is important to consider psychological enablers and barriers to health. Exploring the impact of patient attire has largely been ignored and thus deserves more attention. Though it may seem basic, as highlighted previously, what one wears can impact one's identity, mental health and ultimately health and wellbeing outcomes. As well as raising awareness about the impact patient attire has on patient healthcare experiences, this research hopes the findings will support providers to reflect on wider everyday practices within the services they provide and ask questions about whether they are facilitating a health promoting environment where patients' needs guide their decisions and actions.

## Aims and Hypotheses

This study aims to investigate the impact of wearing a patient hospital gown on the patient experience, specifically focusing on dehumanisation. The study will also look at the impact of wearing a patient gown on the patient-doctor relationship, and patient behaviour.

Given previous research findings, it can be hypothesised that the participants wearing patient hospital gowns will report more thoughts and emotions around the loss of identity, power, and dignity as well as greater identification with the sick role, compared to those participants wearing their usual clothes.

It is also hypothesised that participants wearing gowns will behave in similar ways to a subordinate, relinquishing more power to the physician, than participants wearing their usual clothes, as measured by the language used by the participants. Physiological levels of arousal in participants wearing a patient gown may be higher than those of participants in their usual clothes, as measured through blood pressure readings.

## 156 Method

### 157 Study Design

158 The study will be a randomised controlled trial in which participants will be allocated to  
159 either wear a patient gown or their usual clothes before participating in an hospital admission  
160 interview with a doctor. The study will be pre-registered with the Australian New Zealand  
161 Clinical Trial Registry.

### 162 Eligibility Criteria

163 To be included in the study participants will have to be at least 18 years of age or older, and  
164 be able to speak, read and write in English. Participants will be required to attend the hospital  
165 admission interview in-person at The Auckland University Grafton Campus. Individuals  
166 requiring a support person to attend the admission interview with them will be excluded from  
167 the main analysis, since the presence of a support person may impact outcomes.

### 168 Study Outcomes

169 The primary outcome of this study will be the level of dehumanisation experienced by the  
170 participant following the admission interview. This will be measured via administration of a  
171 questionnaire. The questionnaire has been developed by the investigators of this proposed  
172 study, named the “The Patient Experience and Feedback Questionnaire,” to measure the  
173 presence of factors proposed to contribute to the experience of dehumanisation for patients in  
174 the healthcare setting.

175 The secondary outcomes of this study will be the impact on patient behaviour. Specifically,  
176 the language participants use during the interview to communicate with their doctor will be  
177 analysed. To do this, the interview audio will be recorded, transcribed, and used with the  
178 Linguistic Inquiry and Word Count (LIWC) software. The doctor will measure patient vital

signs as part of the standard admission history taking and examination process. The blood pressures of participants taken during the interview will be looked at as a secondary outcome.

## Sample Size

A power analysis was carried out using G\*Power software with a power level of .80 and a two-tailed significance level of  $\alpha = .05$ , with an effect size of  $d = 0.70$ . Using these parameters gives a required total sample size of 68. The lack of previous experimental data on gown wearing made an estimation of expected effect size more challenging. Research on the effects of submissive posture on self-esteem and first-person pronouns has demonstrated effect sizes of  $d = 0.79$ , and  $d = 1.16$  (Nair et al., 2015). Given the study is cross-sectional, attrition does not need to be accommodated, but we will recruit 70 participants in case of missing data.

## Recruitment

70 participants will be recruited from within The University of Auckland via flyers, student email lists, online advertising, and in-lecture announcements. To ensure fair representation of all ethnic groups in the study, coordinators of the Māori and Pacific Admission Scheme (MAPAS) and Tuākana programs will be contacted to prioritise the inclusion of Māori and Pacific participants proportional to the NZ population. Those who respond to the advertisement will be sent a participant information sheet and checked to see if they meet the eligibility criteria before enrolling in the study. Once enrolled in the study, participants will be contacted via email with details about the experiment dates, times, and locations. Written consent of participants to partake in the study will be gained upon arrival at the study venue.

## Study Procedure

The randomised control trial will be a single-centre study conducted at The University of Auckland Grafton Campus. The 70 participants for the trial will be recruited at The

203 University of Auckland via online, email, and poster advertisements. The participants will be  
204 told that the study is looking to evaluate two different types of medical interviews and that  
205 they will be supporting the researchers in this evaluation via the provision of feedback.

206 Once the potential participants respond to the advertisements for the study via email, a  
207 participant information sheet with study details will be sent to them. Upon meeting eligibility  
208 criteria participants will be asked to register via an online booking system to attend a medical  
209 interview at a date and time convenient to them. Participants will have a selection of dates  
210 and times available to choose from.

211 Once participants arrive at the research venue, they will be asked to read and sign a written  
212 consent form and be given the opportunity to ask any questions they may have about the  
213 study. Participants will also complete a baseline questionnaire collecting demographic details.  
214 Once paperwork is complete, participants will be randomised to either wear a patient hospital  
215 gown or remain in their own clothes. The researcher completing the pre-interview process  
216 with participants will be blinded to the randomisation process and will only know which  
217 group the participant will be in after opening a sealed envelope with the information post pre-  
218 interview procedures. The randomisation will be completed using randomiser.org by the  
219 second researcher who will not be present at the research venue during the interviews.

220 After randomisation of the participants to either the gown wearing or wearing own clothes  
221 group, participants will enter the medical interview room to meet the doctor and begin the  
222 interview. The medical interviews will be carried out by either a female or male 5th or 6th year  
223 medical student from The University of Auckland. The medical students will be employed by  
224 the research team to conduct the interviews. The “doctors” too will be told that they are  
225 supporting a study looking to evaluate two different types of medical interviews. Their role  
226 will be to conduct the interview following a script provided by the researchers. The medical

227 students will be asked to wear what they would normally wear for hospital ward rounds. They  
228 will also be asked to sign a confidentiality statement requiring them not to discuss the study,  
229 the participants or share their thoughts about the interview styles with others and each other.  
230 The medical interview will follow a standard interview structure and finish by taking the vital  
231 signs (Lichstein, 1990). Participants will receive either the female or male doctor depending  
232 on which date and time they book their interview for via the online booking system. The  
233 interview times available on the online booking system will reflect availability of the  
234 employed medical students and the researcher.

235 During the medical interview, participants will be asked to answer questions truthfully.  
236 Participants will not have a specific presenting complaint to share with the doctor. If the  
237 “doctors” have any concerns about the health and wellbeing of the participants following the  
238 interview, they will be asked to share these with the researcher who will be able to take the  
239 necessary steps to ensure the participant is followed-up, informed and given an opportunity to  
240 seek professional support.

241 During the interview, the conversation between the participant and doctor will be recorded  
242 using a voice recorder. This data will later be transcribed and analysed using LIWC post-  
243 interview. The blood pressure of participants will also be measured as part of taking the vital  
244 signs. After completing the interview with the doctor, participants will be asked to complete  
245 The Patient Experience and Feedback Questionnaire.

246 It is expected that the participants will spend a total of 40 minutes at the clinical research  
247 centre. This will include 10 minutes upon arrival spent gowning up if required and  
248 completing the baseline questionnaire. The patient-physician consultation is expected to take  
249 no more than 20 minutes followed by 10 minutes to complete the post-interview

250 questionnaires. Participants will receive a \$20 Countdown voucher as a gesture of gratitude  
251 for volunteering their time for the study as they leave the venue.

252

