## 277 Statistical Analysis

278 IBM SPSS software will be used to analyse quantitative data collected from the trial.

279 Independent t tests will be used to identify differences between the two groups for self-report  
280 measures and blood pressure. ANCOVA analysis will be conducted to control for covariates  
281 known to affect outcomes.

282 All results obtained will be considered statistically significant if  $p$ -values  $< .05$ . The results  
283 will be analysed and reported as described in the consolidated standards of reporting trial  
284 (CONSORT) guidelines to maintain transparency.

285

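### Interviewer is fixed by the booked slot before allocation, but is not named as a stratification factor and is ignored by the stated t test, which gives up some balance and precision

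*Protocol*

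**What the plan says.** **Who interviews.** Under Study Procedure, a female or a male senior medical student plays the doctor, working from a script supplied by the researchers. The number of students employed is not given. Assignment is not random: "Participants will receive either the female or male doctor depending" on the slot booked online, and the slots on offer follow the availability of the students and the researcher.

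**How arms are allocated.** The same section says: "The randomisation will be completed using randomiser.org by the" second researcher, who is off site. The result is in a sealed envelope opened after the pre-interview paperwork. Ratio, blocking, number of lists and stratification are not mentioned.

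**What the interviewer touches.** The primary questionnaire (Measures, Primary Outcome) asks what participants felt and thought during that interview. The interviewer measures the blood pressure (Blood Pressure) and is the other speaker in the recording used for the language outcome.

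**Analysis.** Statistical Analysis says: "Independent t tests will be used to identify differences between the two groups for self-report" measures and blood pressure. It adds an ANCOVA for covariates that affect outcomes, without naming them. No test is named for language. Interviewer is not among the items in the Baseline Questionnaire.

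**Size.** Sample Size takes a two-tailed 5% level "with a power level of .80 and a" standardised effect of 0.70. It "gives a required total sample size of 68", and then "we will recruit 70 participants in case of missing data".

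**The concern.** The primary outcome is a rating of an encounter, and the interviewer is half of that encounter. Manner, sex, dress and measurement technique can all differ between students. The Protocol asks the students to wear their usual ward-round clothes, although its Introduction argues that doctors' attire changes how patients see them. Interviewer is also tied to day and time through the booking system.

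A factor that plausibly affects the outcome and is known before allocation is a natural one to balance and to fit. If it is neither balanced nor fitted, one arm can by chance meet one interviewer more often, and the variance between interviewers stays in the error term. The trial has two participants more than its own calculation requires, so it has little power to spare.

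**Working it through.** **Inputs from the Protocol (Sample Size):** d = 0.70, two-sided alpha .05, power .80, N = 68 required, 70 recruited.

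**Assumptions, because the documents are silent:**
- 1:1 allocation.
- Two interviewers with 35 participants each.
- A difference g between interviewers, in within-interviewer SDs, of 0.3, 0.5 or 0.8.

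**1. The plan's own figure.** Power comes from the noncentral t distribution with noncentrality d × √(n₁n₂/(n₁+n₂)) and n₁+n₂−2 degrees of freedom.
- 33 per arm: .7997.
- 34 per arm: noncentrality 0.70 × √17 = 2.886, power .8116. The total is 68, as stated.
- 35 per arm: noncentrality 0.70 × √17.5 = 2.928, power .823. This is the reference value below.

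**2. Chance imbalance without stratification.** With arms fixed at 35/35, the number x in the gown arm who meet one interviewer is hypergeometric (70, 35, 35).
- Variance of x = 35 × ½ × ½ × 35/69 = 4.438.
- The between-arm difference in share is (2x − 35)/35, with SD 2 × √4.438/35 = .120, or about 12 points.
- The difference is 20 points or more with probability .151. It takes only odd multiples of 1/35, so the next value above 20 points is 25.7; the probability of exceeding 20 points is .055.
- With simple (unrestricted) randomisation the SD is .121 and the probability of exceeding 20 points is .11.
- With a 21/49 interviewer split and fixed arms the SD is about 11 points, and a difference of 20 points or more has probability .12.

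A 20-point imbalance moves the unadjusted estimate by 0.20 × g, that is 0.06, 0.10 or 0.16 SD.

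**3. Validity.** In 40,000 simulated trials per setting with no gown effect, the unadjusted t test rejected in .049, .050 and .049 of trials for g = 0, 0.5 and 1.

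**4. Precision.** With an even split, interviewers add g²/4 to a within-interviewer variance of 1, so the total variance is v = 1 + g²/4. The share due to interviewer is R² = (g²/4)/v. The answer depends on which SD the 0.70 refers to, and the Protocol does not say.

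| g | v | R² | d on total SD: unadjusted → adjusted (effective d = 0.70√v) | d on within-interviewer SD: unadjusted (effective d = 0.70/√v) → adjusted | N for .80 unadjusted, within-interviewer SD |
|---|---|---|---|---|---|
| 0.3 | 1.0225 | .022 | .823 → .831 (0.708) | .815 (0.692) → .823 | 68 |
| 0.5 | 1.0625 | .059 | .823 → .845 (0.722) | .800 (0.679) → .823 | 72 |
| 0.8 | 1.1600 | .138 | .823 → .875 (0.754) | .764 (0.650) → .823 | 78 |

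The adjusted figures use 67 degrees of freedom. The lost degree of freedom costs almost nothing: at g = 0, power is .8228 against .8230.

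**5. What stratification adds to adjustment.** The adjusted figures in step 4 assume that arms are balanced within interviewer. In the simulation with 35/35 arms but no stratification, adjusted power was .816 at g = 0.5 and .815 at g = 1, against .823 with balance. Stratifying is therefore worth somewhat under one point of power. Most of the gain comes from the model term.

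**The case against.** Four points on the other side have weight.

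- **An adjusted analysis is planned.** The ANCOVA's covariates are unnamed, and such a list is commonly left to a statistical analysis plan, which is not at hand. A reader might infer that the plan rules out accounting for interviewer. It does not, and this objection stands. What remains is that the only named test for self-report measures and blood pressure is unadjusted. Stratification, moreover, has to be settled when the envelopes are prepared, not at analysis.
- **Silence is not a statement.** A reader might infer a single unstratified list. The Protocol says only that a web randomiser and sealed envelopes are used. The supportable claim is that interviewer is not named as a stratification factor.
- **Randomisation protects the comparison.** A reader might infer that the gown effect is confounded with interviewer. The interviewer is fixed before a random allocation is revealed, so any imbalance is due to chance and the t test's standard error already allows for it. The type I error in step 3 confirms this. The objection stands in full: the loss is of precision only.
- **The interviewer effect is assumed.** The common script and standard interview structure may keep it small. At 0.3 SD the gain is under one point of power. This stands too, and it limits the size of the point.

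Two further limits apply. No test is named for language, so its analysis cannot be said to ignore interviewer. Two interviewers is a reading of the text, not a stated number.

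**Conclusion.** The point holds as an inexpensive improvement, not as a flaw that threatens the result. Interviewer is known before allocation and plausibly bears on the outcomes; it is not named for stratification, and the stated t test for self-report measures and blood pressure leaves it out.

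The price is modest. At an assumed interviewer difference of 0.3 to 0.5 SD it is about 1 to 2 points of power on either scaling of d. At 0.8 SD it is 5 to 6 points. On the within-interviewer scaling, a difference of 0.5 SD uses up the margin from the two extra participants (power .7997), and 0.8 SD takes power below the planned .80. The imbalance probabilities rest on 1:1 allocation and two interviewers; an uneven split makes imbalance somewhat less likely.

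The change is worth making because it costs so little and because the stratification part cannot be added once enrolment has begun.

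**What to change.** 1. Stratify the randomisation by interviewer: one list and one envelope stack for each, in permuted blocks of varying size, prepared by the same off-site researcher.
2. Record the interviewer for every participant.
3. Replace the plain t test for the primary outcome and blood pressure with a linear model that has arm and interviewer as fixed factors, and use the same interviewer term in the language analysis. The term should accompany the stratification: a t test that ignores a stratification factor tends to overstate the standard error.
4. State how many interviewers are employed. If there are more than two, use one list and stack for each.

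The cost is an extra list and envelope stack, one term in the SPSS model, and one degree of freedom for each interviewer beyond the first. No additional participants or staff are needed.
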